# Efficacy of adjunctive intensive transcranial direct current stimulation of different cortices in treatment-resistant depression: a study protocol for a randomized double-blinded sham-controlled trial

**DOI:** 10.1186/s12888-022-04465-2

**Published:** 2022-12-19

**Keywords:** Treatment-resistant depression (TRD), Transcranial direct current stimulation (tDCS), Dorsolateral prefrontal cortex (DLPFC), Orbitofrontal cortex (OFC), Biomarkers, Resting-state functional magnetic resonance imaging (rs-fMRI)

## Abstract

**Background:**

Treatment-resistant depression (TRD) carries a high economic burden worldwide. Transcranial direct current stimulation (tDCS) is advantageous for improving cognition and can be safely used in the treatment of depression. The effectiveness of tDCS of the left and right orbitofrontal cortex (OFC) as adjuvant treatment in patients with TRD has rarely been explored. Therefore, the objective of this trial is to evaluate the effectiveness there of when administering left dorsolateral prefrontal cortex (DLPFC) positive stimulation or OFC negative stimulation in patients with TRD.

**Methods:**

Ninety eligible participants will be recruited to receive intervention at Shanghai Mental Health Center. Treatment will be randomly assigned in a double-blind fashion. Participants will receive either DLPFC (*n* = 30), OFC (n = 30), or sham (n = 30) tDCS, while continuing their usual pharmacotherapy at a stable dosage for at least 2 weeks before enrollment and throughout the stimulation period. All participants will receive 20 weekday stimulation sessions of 60 minutes duration each. Participants in the active group will be stimulated at 2 mA throughout the session, whereas the sham group will receive only a brief period of stimulation to mimic the sensation. After 20 stimulation sessions, no further treatment will be administered. Measurements will be conducted at regular points throughout and at 8 weeks after trial completion. The primary outcome is the change in the 17-item Hamilton Depression Rating Scale (HAMD-17) score after 20 sessions. Secondary outcomes were defined as changes in other measurement scales, cognitive function, resting-state functional magnetic resonance imaging (rs-fMRI), and serum biomarkers.

**Discussion:**

We hypothesize that, in contrast to the sham group, both the active DLPFC and OFC tDCS groups will show superiority in HAMD-17 score reduction after 5, 10, and 20 sessions. Moreover, associations of the improvement of depressive symptoms with variations in rs-fMRI and TRD-related biomarkers will be evaluated. Our study may suggest that adjunctive intensive tDCS with left DLPFC positive stimulation or right OFC negative stimulation may be effective as a novel method to relieve depressive symptoms in patients with TRD. The variation of rs-fMRI, biomarkers could be used as a potential prediction model of treatment efficacy in TRD.

**Trial registration:**

The trial protocol is registered with www.chictr.org.cn under protocol registration number ChiCTR2200058030. Date of registration: March 27, 2022. Recruitment started in September 2022 and is ongoing.

## Background

The World Health Organization ranks major depressive disorder (MDD) among the most debilitating diseases to society, partly due to its association with increased utilization of healthcare resources, diminished quality of life, and indirect personal and societal costs [1]. More than 50% of patients with MDD do not reach remission with initial treatment; of those 30–50% are unresponsive to treatment [2]. The designation “treatment-resistant depression (TRD)” is used to describe patients who do not respond to antidepressant therapy despite the use of appropriate dosages in one or more adequate trials of at least 6 weeks duration [3], which contributes to a disproportionately high burden of illness. The treatment of choice hereafter has traditionally been electroconvulsive therapy (ECT). Although effective, this method of neuromodulation can have a deleterious effect on the cognitive function of patients during the course of treatment [4].

Another promising neuromodulatory method that may be used in this scenario is transcranial direct current stimulation (tDCS). Unlike ECT, tDCS consists of the application of a low-intensity current for longer periods (typically 20–30 min) through electrodes that are applied to the scalp. Previous results have suggested that tDCS may be an effective treatment for MDD; however, its role in treating TRD remains unclear. A meta-analysis by Brunoni et al. (2016) [5] found that the likelihood of response to tDCS was positively correlated with treatment duration and dose but negatively correlated with treatment resistance (defined as a failure to respond to two previous trials of antidepressants). To date, some studies [6–10] have specifically examined the use of tDCS in patients with TRD; all were limited by their small sample sizes and relatively low-intensity protocols, among other methodological issues.

The dorsolateral prefrontal cortex (DLPFC) is the most common stimulation target for tDCS in the treatment of MDD and its antidepressant efficacy has been confirmed. To date, the orbitofrontal cortex (OFC) has been found to be a promising new target for the treatment of depression due to its role in behavioral decision-making, emotion regulation, and reward [11]. Hyperactivation of the right OFC and enhanced connectivity with other cerebral regions, which could present as suicide attempts, emotional lability, or lack of pleasure, might be functional mechanisms of TRD. Thus, targeted inhibition of the right OFC and its connectivity with other cerebral regions may be effective in TRD.

Moreover, advances in resting-state functional magnetic resonance imaging (rs-fMRI) have enabled the examination of the plasticity of large-scale networks using blood oxygen level-dependent correlations measured at rest. Resting-state functional connectivity analysis provides unique insights into experience-dependent brain plasticity in humans [12]. Analysis of cortical excitability and functional connectivity based on rs-fMRI, combined with clinical characteristics and TRD-related biomarkers, could provide a predictive model of DLPFC-tDCS or OFC-tDCS, and thus, could contribute to a targeted and individualized treatment plan for patients with TRD.

## Methods

### Objectives

The primary objective of this study is to investigate the efficacy of a 4-week treatment of intensive adjunctive tDCS with left DLPFC positive stimulation or right OFC negative stimulation on depressive symptoms as measured by the 17-item Hamilton Depression Rating Scale (HAMD-17).

The secondary objectives are as follows:To investigate the effects of adjunctive treatment of TRD with intensive tDCS on cognition, measured by the Wisconsin card sorting test (WCST) and Stroop color–word test (SCWT).To investigate the effects of adjunctive treatment of TRD with intensive tDCS on variations in nerve growth factor (NGF), brain-derived neurotrophic factor (BDNF), glial cell line-derived neurotrophic factor (GDNF), interleukins (IL), tumor necrosis factor-alpha (TNF-α), and its soluble receptors sTNFr1 and sTNFr2 in blood plasma.To investigate the effects of combined treatment of TRD with intensive tDCS on the variation of neuronal activity in the cerebral cortex as measured by rs-fMRI.

### Trial design

We have adopted a randomized allocation design to test sham-controlled antidepressant augmentation. Patients with TRD will continue maintenance pharmacotherapy for at least 2 weeks before stimulation initiation and during the entire stimulation period. Groups will be randomized through random code generator software (www.randomization.com) at a ratio of 1:1:1 into one of the following three groups: active DLPFC tDCS group, active OFC tDCS group, or sham tDCS group. The total study duration will be 12 weeks (Fig. 1).

**Fig. 1 Fig1:**
[figure not shown]
Trial flowchart. We plan to recruit 90 patients with TRD. Participants are required to continue maintenance pharmacotherapy from at least 2 weeks before stimulation intiation and throughout the stimulation period

### Recruitment

We will approach patients in the Shanghai Mental Health Center outpatient and inpatient units. Our inpatient and outpatient care units follow up at least 10,000 patients with MDD each year, 20% of which are treatment-resistant. Considering the inclusion and exclusion criteria, we expect to approach 100 patients to reach the recruitment target of 90 patients. Usual clinical care will be maintained for all participants following the completion of the trial at our care unit. Recruitment, pre-participation screening, allocation, intervention, and data collection will be conducted between September 2022 and March 2024. We plan to conclude the study and have the results available for analysis at the end of 2024. The present study protocol complies with the SPIRIT 2013 recommendations (Standard Protocol Items: Recommendations for International Trials) [13]. Figure 1 shows the schedule of enrollment, interventions, and assessments.

### Eligibility criteria

#### Inclusion criteria

Ability and willingness to provide written informed consent to participate in the trial and undergo all necessary procedures;Age from 18 to 65 years;A diagnosis of MDD according to the Diagnostic and Statistical Manual of Mental Disorders, Fifth Edition (DSM-5), which is assessed by at least one professional psychiatrist;Han ethnicity;Right-handedness;Adequate auditory and visual ability to complete the necessary checks;A HAMD-17 score ≥ 17 [14];Insufficient response (response rate < 50%, and a reductive ratio of HAMD-17 < 50%) to two antidepressants with different mechanisms of action for at least 6 weeks at an adequate dose (e.g., clomipramine ≥150 mg/day, fluoxetine ≥20 mg/day) during the current episode;Willing to remain on maintenance pharmacotherapy for at least 2 weeks before the stimulation initiation and during the total stimulation period.

#### Exclusion criteria

The presence of severe systemic illnesses including, but not limited to severe hepatic, renal, endocrine, cardiovascular, respiratory, hematological or oncological diseases, deemed by the investigator to be unsuitable to allow participation in the trial;Any clinically significant abnormal laboratory examination that may influence the health of participants in the opinion of the investigator;A history of any significant medical illness such as neurological disorders (e.g.: cerebral trauma, seizure disorder, etc), which in the opinion of the investigator would preclude safe participation in the trial;Known with current psychosis as determined by the DSM-5; or a history of a non-mood psychotic disorder;Current alcohol and/or any illicit or legal drug abuse;Current or planned pregnancy and/or lactation during the trial;An abnormal scalp such as open wounds;A score = 4 for item 3 (suicide) on the HAMD-17;Having had or currently receiving modified electroconvulsive therapy (MECT) or repetitive transcranial magnetic stimulation (rTMS) in the past 1 month;Participation in another clinical trial concurrently or less than 1 month prior to randomisation.

### Interventions

Participants will receive one of three interventions: active DLPFC tDCS, active OFC tDCS, and sham tDCS. tDCS-CT devices (Neuroelectrics, Starstim 8, USA) will be used for brain stimulation. The anode and cathode electrodes will be inserted in saline-soaked sponges with a diameter of 3.2 cm and then positioned over the left and right DLPFC and OFC simultaneously while using a specific headgear [15] to maintain the double blind. The current will pass through the anode and cathode corresponding to the left and right DLPFC in the active DLPFC tDCS group and the left and right OFC in the active OFC tDCS group, respectively. For the sham group, the current will be rapidly increased up to 2 mA over the first 30 s then rapidly ramped down to 0 mA over the next 30 s automatically to allow participants to feel the typical initial sensations of active tDCS. At each session, a 2 mA current will be applied for a duration of 60 min. Participants will receive a total of 20 sessions, which will be conducted daily on weekdays. Trained psychiatrists and psychologists who will be blinded to the group assignments, will administer the tDCS regimen. After completing the 20 sessions, no additional stimulation treatment will be administered.

### Discontinuation or modifications

Participants can leave the study at any time for any of the following reasons:If participants do not meet the inclusion criteria;If participants or their guardians decide to leave the study;If participants develop a serious physical disease whether or not it is related to tDCS;If participants stop taking their medication for three consecutive days, stop effective contraception, or become pregnant;If participants use other treatments (including MECT, rTMS);If other conditions occur, and the investigator decides to terminate the study;If the participant fails to comply with the study procedures.

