### Statistical methods

Descriptive analyses will consist of means and SD for continuous variables and percentages for categorical variables. Data normality will be tested with the results expressed as mean ± SD or percentage, whenever appropriate. Nonparametric tests are to be used if the data are not normally distributed. Baseline variables will be compared between the groups using either the Student’s t-test or chi-squared test (e.g., sociodemographic data, cognitive function data, biomarkers representing inflammatory mechanisms associated with TRD, and response and remission rates among groups). To compare the primary endpoint, a two-way ANOVA will be used, considering the group (intervention and sham control groups) and time points (pre- and post-intervention), followed by the Bonferroni post hoc test, in case of significant F-ratios. A mixed-effects model for repeated measures will analyze changes from baseline HAMD-17 scores, time, and their interaction. Pretreatment values (e.g., age, sex, baseline HAMD-17, and biomarker levels) will be adopted as covariates to correct for possible differences. An intention-to-treat analysis will be conducted, that is, all participants will be included in the final analysis regardless of adherence to the intervention. No additional analyses will be performed for this study. All calculations are to be performed using R software (version 4.1.3), and the significance level is set at *p* ≤ 0.05.

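### The withdrawal list does not separate stopping stimulation from leaving the study, which undercuts the promised analysis of all participants regardless of adherence

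*Protocol article*

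**What the plan says.** The section Discontinuation or modifications has one list, introduced by "Participants can leave the study at any time for any of the following reasons". Four of its entries matter here:

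- "If participants use other treatments (including MECT, rTMS"
- "If participants stop taking their medication for three consecutive days"
- "If the participant fails to comply with the study procedures"
- "If participants do not meet the inclusion criteria"

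The section does not mention stopping stimulation while staying in follow-up. It does not say whether HAMD-17 ratings continue after any of these events.

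Statistical methods says: "An intention-to-treat analysis will be conducted, that is, all participants will be included in the final analysis regardless of adherence to the intervention". The primary endpoint is to be compared by a two-way ANOVA with group and pre/post time as factors. In addition, "A mixed-effects model for repeated measures will analyze changes from baseline HAMD-17 scores, time, and their interaction". The same section rules out any further analyses. Data collection methods places the on-treatment HAMD-17 ratings at weeks 1, 2 and 4. Sample size allows for 20% dropout.

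**The concern.** The participants whose non-adherence is supposed not to matter in the analysis are the ones whom the withdrawal list lets out of the study. This is a rule of trial conduct working against a stated analysis. An analysis plan can choose how to handle missing values, but it cannot recover a week-4 rating that was never taken.

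The losses are also unlikely to be random. Patients plausibly turn to MECT or rTMS when they are not improving, and that may happen more often on sham. If so, the sham patients who remain look better than the sham group as randomised, and the active-versus-sham difference is understated. Because the article excludes further analyses, the plan as written has no sensitivity analysis to show how much such losses matter.

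**Working it through.** **The plan's own dropout figure.** 72 × 1.2 = 86.4, rounded up to 87, as stated. The planned 90 with 20% loss gives 90 × 0.2 = 18 lost and 72 remaining, or 24 per group. Loss on this scale is therefore expected by the plan itself. The article gives no reasons for dropout and no rates by arm.

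**What each analysis can do with a participant who leaves and is not rated again:**

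| Time of leaving | Pre/post ANOVA | Mixed model of change |
|---|---|---|
| Before week 1 | No post value | No change score |
| After week 1 or 2, before week 4 | No post value | Kept through the early ratings, if missing at random |
| After week 4 | Complete | Complete for the primary time point |

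**Size of the bias among completers.** Let a share p of an arm leave, and let r be the correlation between outcome and the tendency to stay. With a normal outcome, the mean of those who stay exceeds the mean of the arm by

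shift = r × SD × φ(z) / (1 − p), where z is the normal quantile of p.

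*Upper bound.* Take r = 1 in sham (exactly the worst responders leave) and random loss in the active arms:

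- p = 0.20: φ(0.842)/0.8 = 0.280/0.8 = 0.35 SD
- p = 0.10: 0.1755/0.9 = 0.195 SD

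For scale, with 24 per group, 80% power and an assumed two-sided 0.05, the detectable difference is about 0.83 SD.

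*Imperfect selection.* Assumed: SD 0.25, true difference in reductive ratio 0.20, r from 0.3 to 0.7 and the same in both arms. The figure 0.25 stands in Sample size without a unit, so applying it to the reductive ratio is an assumption. The 0.20, the values of r and the arm-specific losses are also assumed.

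- 30% leave sham, 10% leave active: 0.3477/0.7 − 0.1755/0.9 = 0.497 − 0.195 = 0.302. Times 0.25 = 0.0754. Times 0.3 to 0.7 = 0.023 to 0.053. The difference falls from 0.20 to between 0.177 and 0.147.
- 25% leave sham, 15% leave active: 0.3178/0.75 − 0.2332/0.85 = 0.424 − 0.274 = 0.149 after rounding. Times 0.25 = 0.0373. Times 0.3 to 0.7 = 0.011 to 0.026. The difference falls to between 0.189 and 0.174. A simulation with 400,000 per arm gave 0.189 to 0.173.
- 20% leave each arm: the two terms cancel, and the difference stays at about 0.20.

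The shrinkage with unequal loss is thus roughly 0.01 to 0.05, or 0.04 to 0.21 in SD units. The SD-unit figures depend on neither the assumed SD nor the assumed true difference.

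**The case against.** The best defence is that the article says less than the concern needs. The list says that participants may leave, not that they must, and it is silent on later ratings. The schedule table is not visible, and a condensed article may leave follow-up after discontinuation to the full protocol. This stands to the extent that the end of ratings is an inference. It remains the natural reading of leaving a study, and the only status the section describes is leaving.

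Three stronger readings are tempting, and the documents do not support them.

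- *That the intention-to-treat analysis is impossible.* The mixed model keeps anyone with a week-1 or week-2 rating, and those who leave after week 4 already have the primary value. The analysis is weakened, not ruled out.
- *That patients who improve must leave, because a HAMD-17 of at least 17 is an inclusion criterion.* This would defeat the trial's own definitions of response and remission, which require large falls in the score. The eligibility entry is more naturally read as covering participants found to have been wrongly enrolled. Removing them after randomisation would still sit badly with an analysis of all participants, but it is not clearly related to outcome.
- *That a shift of 0.35 SD is to be expected.* It requires perfect selection in sham, random loss in the active arms, and the whole 20% allowance in sham being outcome-driven. The article supports none of these.

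One could also say that other treatment and missed medication are not adherence to the intervention in the strict sense. That does not remove the conflict, because the sentence promises to include all participants.

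**Conclusion.** The point holds as a conflict between two sections that should be reconciled. Grounds that include other treatment, missed medication and non-compliance lead out of the study, while the analysis promises everyone regardless of adherence. Followed on the natural reading, this loses week-4 ratings that are plausibly related to outcome. The pre/post ANOVA then drops these participants, and the mixed model leans on a doubtful missing-at-random assumption.

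If poor responders leave sham more often than the active arms, the bias is toward no difference. It is at most 0.35 SD when 20% of sham leave and active losses are random. Under the assumed imperfect selection and unequal loss it is roughly 0.01 to 0.05 on a true difference of 0.20. It is close to nil if loss and selection are alike across arms. These are completers-only figures; the mixed model would recover part of the bias where early ratings exist. The direction and size rest on arm-specific losses that the article does not give, so they are illustrations, not predictions.

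**What to change.** Reconcile Discontinuation or modifications with Statistical methods:

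1. Separate discontinuation of stimulation from withdrawal from follow-up.
2. State that every randomised participant who stops stimulation, is non-adherent, starts another treatment or is found ineligible after randomisation is still rated on HAMD-17 at the scheduled visits, unless they decline further assessment.
3. Record the date and type of any other treatment. A rating taken after MECT or rTMS reflects that treatment as well, and the record lets the analysis show this.
4. State that all of these participants stay in the intention-to-treat analysis.

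The cost is a formal amendment, which the article already requires for any change, and a few extra ratings. If loss runs at the planned 20%, at most about 18 of 90 participants are concerned. No clinical criterion for stopping stimulation is changed or proposed.

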### Outcomes

Primary outcome: The reductive ratio of HAMD-17 after 4 weeks, as well as after 20 sessions.

Secondary outcomes: The changes in other clinical assessments such as the Young Mania Rating Scale (YMRS), Clinical Global Impression Scale (CGI), cognitive function, biomarkers representing potential mechanisms associated with TRD, and neuronal activity measured using rs-fMRI.

### Sample size

The sample size was calculated based on the data from O’Doherty et al. (2001) [11] and Cieslik et al. (2013) [16]. In these studies, active tDCS was assumed to be superior to sham tDCS in controlling depression with a conservative mean difference of 0.65 and standard deviation (SD) = 0.25. We set a type 1 error α (significance) and a power of 80%. The G power software (V3.1.9.4) was used to calculate the sample size. The results indicated a minimum requirement of 24 participants per group (a total of 72 participants). Accounting for a 20% dropout rate, 87 participants are required for our experiment. Finally, we plan to enroll 30 participants per group for a total of 90 participants.

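### The assumed effect of 0.65 is not linked to TRD or to the OFC arm, is not conservative at 2.6 SD, and does not give 24 per group when one active arm is compared with sham

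*Protocol article*

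**What the plan says.** In the protocol article, the Sample size section opens with "The sample size was calculated based on the data from" two cited studies, [11] and [16]. It then says that in those studies "active tDCS was assumed to be superior to sham tDCS in controlling depression with a conservative mean difference of 0.65". For the spread, the section gives "standard deviation (SD) = 0.25". One value serves both active arms. No unit or outcome scale is attached to 0.65. The error rate is introduced with "We set a type 1 error α (significance) and a power of 80" per cent, with no value for alpha, no sidedness and no test. The result is 24 per group (72 in all), 87 after a 20% dropout allowance, and 90 planned.

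Other sections bear on where this effect comes from:

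- The Background says that "some studies [6–10] have specifically examined the use of tDCS in patients with TRD". It describes those studies as small and of fairly low intensity, and calls the role of tDCS in TRD unclear.
- The Background also reports a meta-analysis in which response to tDCS was "negatively correlated with treatment resistance" and positively correlated with duration and dose.
- The only other use of [11] is in the Background, where the OFC is called a "promising new target for the treatment of depression due to its role in behavioral decision-making, emotion regulation, and reward [11".
- The Abstract says that tDCS of the OFC "as adjuvant treatment in patients with TRD has rarely been explored".
- Outcomes and Data collection methods make the HAMD-17 reductive ratio the primary outcome, with response at a 50% and remission at a 75% reduction.

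**The concern.** A reader who wants to know what the 80% power means has to trace the effect to its source and then from the effect to the sample size. Neither step can be completed. The two cited sources are not among the studies that the protocol presents as tDCS trials in TRD, and nothing connects either of them to OFC stimulation as a treatment. The label attached to the effect suggests caution, yet the stated figures describe a very large difference. The stated effect and SD also do not lead to the stated number per group in the comparison that the section describes.

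At stake is how a non-significant arm can be read. If nobody can say which effect the trial has 80% power to detect, nobody can say what a null result rules out. This matters most for OFC, where the protocol itself says there is little prior work.

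**Working it through.** **Inputs.** Difference 0.65, SD 0.25, power 80%, 24 per group, 20% dropout (Sample size); 1:1:1 allocation (Trial design); significance level 0.05 (Statistical methods). Two-sided testing is my assumption, as is the comparison of one active arm with sham without multiplicity correction.

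**1. The plan's own chain of numbers.** 24 × 3 = 72. Then 72 × 1.2 = 86.4, rounded up to 87. Dividing instead gives 72/(1 − 0.2) = 90, which is the planned enrolment, so the dropout step does no harm. The 24 itself is what needs reproducing.

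**2. The stated effect and SD.** d = 0.65/0.25 = 2.6. By normal approximation, n per arm = 2(1.960 + 0.842)²/d² = 15.70/6.76 = 2.3, so 3. The exact t calculation gives 4. With 24 per arm the power would exceed 99.9%.

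**3. 0.65 read as a standardised difference.** n per arm = 15.70/0.4225 = 37.2, so 38, or 39 by exact t. With 24 per arm the power is 60%. A one-sided 5% test needs 30 per arm, and 24 gives 72%.

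**4. One-way ANOVA with three groups.** Effect size f = 0.25 needs 53 per group and f = 0.65 needs 9. Neither is 24.

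**5. What 24 per arm detects.** Solving the exact t calculation for 80% power gives d = 0.826, about 0.83 SD. If the SD is 0.25, that is 0.826 × 0.25 = 0.207, about 21 percentage points of HAMD-17 reduction. With all 30 per arm analysed, d = 0.736.

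**6. Power over assumed effects.** The documents give no effect size for tDCS in TRD, so this range is illustrative (two-sided 5%).

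| True effect (SD) | 24 per arm | 30 per arm |
|---|---|---|
| 0.3 | 17% | 21% |
| 0.4 | 27% | 33% |
| 0.5 | 40% | 48% |
| 0.65 | 60% | 70% |
| 0.8 | 77% | 86% |

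**7. 0.65 in the unit of the primary outcome.** This is conditional, because the section gives no unit. The mean active reduction equals the mean sham reduction plus 0.65. Sham at 0 gives 0.65, already above the 0.50 that defines response in one patient. Sham at 0.10 gives 0.75, the remission threshold. Sham above 0.35 would need an active mean above 1, which is impossible. Sham patients stay on pharmacotherapy, so some improvement in that arm is plausible.

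**The case against.** Five points can be made for the plan.

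- **The sources cannot be inspected.** A reader might infer that the power claim has no basis at all. The documents do not support that. The Sample size section describes [11] and [16] as active-versus-sham tDCS data in depression, and citing [11] elsewhere for OFC function does not show what else it contains. The list [6–10] is introduced as some studies, not as complete. What stands is that the protocol does not show the link.
- **The Background points both ways.** A reader might infer that the label contradicts the protocol's own evidence, since response falls with resistance. The same sentence says that response rises with duration and dose, and this trial uses 60-minute sessions against a typical 20–30. So there is no outright contradiction. But mixed evidence and a role described as unclear do not justify the label either, and 2.6 SD does not fit it.
- **Other settings can reach 24.** Some repeated-measures ANOVA settings for three groups do so on the between-group test, for example f = 0.25 with four time points and correlation 0.25, or f = 0.325 (half of 0.65) with two time points and correlation 0.5. The protocol states none of these inputs, so the number may have a valid origin, but not one that can be recovered from the text.
- **The trial may be large enough.** If the SD really is 0.25 on the ratio scale, 24 per arm detects 0.21, about a third of 0.65. The low powers in the table come from assumed effects. It cannot be concluded that the trial is underpowered.
- **No misreading is announced.** A reader might infer that a null arm would be presented as an adequately powered negative. No section says so, and the article promises publication whatever the result.

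A journal article may leave detail to a fuller document. The point here concerns what the article does state: a source, an effect, an SD and a label.

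**Conclusion.** The point holds in this form. The effect is attributed to two references outside the studies that the protocol names for tDCS in TRD, with no link shown to TRD or to OFC stimulation. Calling 2.6 SD conservative is not supportable. The stated effect does not produce 24 per group in a two-arm comparison: about 4 are needed as written, 39 if 0.65 is already standardised. With 24 per arm, 80% power is reached at about 0.83 SD.

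These figures assume a two-sided 5% test of one active arm against sham without multiplicity correction. The 0.21 further assumes that the SD of 0.25 is on the reductive-ratio scale. The conclusion does not extend to the claim that 90 patients are too few, because the documents give no effect for TRD or OFC against which to judge that. Nor does it extend to the claim that no estimate exists for OFC in TRD: the Abstract says only that it has rarely been explored.

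**What to change.** Reword the Sample size section and keep 90 patients:

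- Delete the word conservative.
- State the unit of the effect, the effect, the SD, alpha, sidedness, the test and the software settings actually used.
- Give a traceable source for the effect in TRD, or call it an assumption. Do this separately for DLPFC and OFC. The studies in [6–10] are a place to look, but the Background's own reservations about their size and intensity mean that they should not be adopted without comment.
- Replace the power claim with the smallest difference that 24 completers per arm can detect (about 0.83 SD at two-sided 5%, before any multiplicity correction), and add power over a range of assumed effects, for example 60% at 0.65 SD, 40% at 0.5 SD and 27% at 0.4 SD.

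The cost is one rewritten paragraph, with no added patients or procedures. The downside is that the stated power may look less favourable.
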